## Assignment of interventions: allocation

### Sequence generation {16a}

A randomization procedure through a computerized system (Research Electronic Data Capture or REDCap) has been established, generated by the data management unit of the clinical trial center Leuven, which ensures the integrity of the trial.

### Concealment mechanism {16b}

In this open-label study, patients are randomly allocated in order of diagnosis using a computerized system (REDCap) applying an unknown allocation sequence.

### Implementation {16c}

The investigators will randomize the patients using a computerized system (REDCap).

## Assignment of interventions: blinding

### Who will be blinded {17a}

As it is an open-label study, the study participants and clinical staff are not blinded.

### Procedure for unblinding if needed {17b}

The clinical staff is not blinded.

## Data collection and management

### Plans for assessment and collection of outcomes {18a}

Trained investigators and CTAs perform data collection daily. All required patient data are available in the patient’s electronic health file. Access to this file and its components is centrally monitored, making sure only the consented data are collected. The clinical scale proposed by the WHO will be used to assess clinical outcomes. The local laboratory of participating sites performs laboratory tests—the central lab tests interleukins in UZ Leuven.

### Plans to promote participant retention and complete follow-up {18b}

An outpatient follow-up is provided after 5–7 weeks with functional, radiographic, and laboratory evaluation, as described above. However, if this is not possible or participants discontinue the study, a short follow-up over the telephone will be suggested alternatively.

### Data management {19}

Data are stored and pseudonymized in the REDCap system allowing for secure and GDPR-compliant data handling.

### Confidentiality {27}

The data are collected, pseudonymized, stored, and managed in the REDCap system. This system allows for secure data management. Access to pseudonymized patient data is logged and only available to those who need data access. Patient data are securely stored in this system for 25 years, keeping up with the high standards of data protection.

### Plans for collection, laboratory evaluation, and storage of biological specimens for genetic or molecular analysis in this trial/future use {33}

Routine laboratory tests will be performed as described above. Citrated plasma leftovers of the samples used for these laboratory tests will be stored in a study-specific area in the University Hospitals Biobank at − 80 °C for future analysis.

## Statistical methods

### Statistical methods for primary and secondary outcomes {20a}

#### Analysis of the primary efficacy endpoint

The primary endpoint will be analyzed using competing risk analyses whereby death without any improvement will be considered as a competing risk. Event rates will be estimated using cumulative incidence functions (CIF). Median times to improvement will be calculated by the treatment group.

The effect of treatment will be assessed by performing a Fine and Gray competing risk regression model that includes the baseline clinical status value on day 0 as a covariate and randomized treatment as a factor. From the Fine and Gray model, the treatment effect and associated 95% confidence interval will be estimated.

In the pilot phase of DAWn-Antico, the effect of modulation of thromboinflammation will be evaluated on a laboratory primary efficacy endpoint, mean D-dimer level at day 6. The null hypothesis being tested is that the mean D-dimer level on day 6 is the same for the standard of care and intervention arm. Means will be compared with appropriate statistical testing after checking for normality. The full statistical analysis plan will be finalized before the database lock.

To evaluate the effect of aprotinin and high-dose enoxaparin vs. anakinra, analyses will be performed separately in patients with or without signs of hyperinflammation (i.e., with or without an indication for anakinra in the intervention group).

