#### Treatment of hyperinflammation

Patients in the intervention arm will be monitored for hyperinflammation. If, at any point during the study, the patient develops signs of hyperinflammation, treatment with anakinra will be started if there are no contraindications (see the “Exclusion criteria” section).

Presence of hyperinflammation is defined as follows:
Absolute lymphocyte count < 1000 cells/mLTwo of the following: (i) ferritin > 800 ng/mL, (ii) LDH > 400 U/L, or (iii) D-dimers > 1000 ng/mL

These lab values have been identified as independent predictors of adverse outcome in patients with severe COVID-19 [2, 4, 22, 23].

Anakinra will be administered by IV infusion at a total dose of 400 mg per day, divided into 4 doses 100 mg IV every 6 h. Anakinra treatment will continue for 15 days, i.e., days 1 to 15. Before administration, the full content of the prefilled, single-use syringe (anakinra 100 mg) will be diluted in 100 mL saline. The IV administration of anakinra has to occur immediately after the preparation over an infusion period of 60 min. Full instructions for the preparation of anakinra are available in the IMP manual. Conditions for storage and injection are described in the attached protocol.

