### Sample size {14}

Sample size estimates provided serve as a reference, but not as an indication of the final number of patients to be randomized.

In the pilot phase of DAWn-AntiCo, we will evaluate the effect of modulation of the thromboinflammatory response on biochemical parameters. To evaluate the effect of this strategy, we will evaluate the difference in mean D-dimers on day 6. Published data show highly variable D-dimer values in patients with COVID [2, 3]. For an estimated mean D-dimer of 1000 with a standard deviation of 600, a sample size of 51 patients (17:34 with 1:2 randomization) has a power of 0.8 and an alpha of 0.05 to detect a difference of 500. We will therefore evaluate the effect of the intervention after a pilot phase of 60 (20:40) patients. Based on the information from other DAWn studies, the final sample size for effect on clinical outcomes will be evaluated following this pilot phase.

In their study comparing clinical improvement rates for lopinavir-ritonavir in hospitalized patients with severe COVID-19, Cao et al. reported a clinical improvement rate in the control group of 37.7% on day 14 [25].

Therefore, for our sample size calculations, we assume that a 40% improvement rate will be observed on day 15 in the control group, which yielded an expected hazard ratio of 1.5632. Since all missing clinical status data up to day 15 will be imputed, we assumed no censoring of the data prior to day 15. Based on the log-rank test, with a 2-sided significance level of 5% and 80% statistical power and using a (2:1) randomization ratio in favor of the intervention, we estimate that a total sample size of 354 patients will suffice to detect an absolute improvement of 15% (i.e., 55% in the intervention group). To detect an absolute improvement of 20% (60% in the intervention group), a total sample of 196 patients will suffice. We propose a pragmatic sample size of 210 patients taking into account early dropouts.

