### Methods in analysis to handle protocol non-adherence and any statistical methods to handle missing data {20c}

Patients who do not have complete clinical status data up to day 15 will be accounted for as follows:
Single-day missing, with preceding and following day known: in these cases, the missing value will be imputed by the maximum of the two surrounding values.Otherwise: missing data will be imputed using multiple imputation methodology whereby a total of 100 imputations will be done. Clinical status on each day will be imputed consecutively based on the clinical status of the previous days and meaningful clinical variables. When all data have been imputed, the cumulative score up to day 15 will be calculated using the imputed scores. Age, gender, baseline disease severity, and randomized treatment group will be included in the imputation model.

Up to the time of death, missing D-dimers will be imputed using a methodology similar to the one described for the imputation of clinical status. If necessary, a log-transformation will be applied to the D-dimer data to attain a normal distribution for D-dimer. After imputation, to account for deaths before day 6, D-dimer data will be analyzed using a GEE model that evaluates the data over time with an appropriate model.

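### The primary Fine and Gray model is valid but leaves out baseline hyperinflammation and age; pre-specifying them could add power at almost no cost

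*Protocol article*

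**What the plan says.** Under Analysis of the primary efficacy endpoint, the Protocol article fixes a Fine and Gray model for time to sustained improvement or live discharge, with death without improvement as the competing risk. The model "includes the baseline clinical status value on day 0 as a covariate and randomized treatment as a factor".

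Three other places bear on which baseline variables matter:

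- Treatment of hyperinflammation defines the state by lymphocyte count, ferritin, LDH and D-dimer, and says of them: "These lab values have been identified as independent predictors of adverse outcome in patients with severe COVID-19".
- Methods for additional analyses {20b} plans separate analyses by hyperinflammation status at randomization, so the status is needed in both arms.
- The missing-data section {20c} states: "Age, gender, baseline disease severity, and randomized treatment group will be included in the imputation model".

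The sample size section {14} rests on a log-rank test "with a 2-sided significance level of 5% and 80% statistical power", "using a (2:1) randomization ratio in favor of the intervention". It gives 354 patients for 40% v 55%, 196 for 40% v 60%, and proposes 210.

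**The concern.** The document singles out certain baseline measurements as predictors, uses them to classify patients, and then leaves them out of the analysis that decides the trial. In a hazard-type model, omitting a covariate that predicts outcome draws the treatment hazard ratio toward 1 compared with its value conditional on that covariate, and this lowers power. Day-0 status is a scale of hospitalization and respiratory support, so it need not capture inflammatory state.

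Power is not abundant here. The proposed 210 patients suit a 20-point difference; the article's own figure for a 15-point difference is 354. An efficiency gain from data already collected would be worth having, and covariates can be added credibly only before results by arm are seen in this open-label trial.

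**Working it through.** **Step 1: the plan's own sample size.** The inputs from Sample size {14} are two-sided alpha 0.05, power 80%, 2:1 allocation, and no censoring before day 15. For the control rate, "we assume that a 40% improvement rate will be observed on day 15 in the control group"; the intervention rate is 55% or 60%. The formulas are:

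- HR = ln(1 − pT) / ln(1 − pC)
- events = (1.960 + 0.842)² / [(1/3)(2/3)(ln HR)²]
- N = events / [(pC + 2pT)/3]

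Results:

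- 40% v 55%: HR = ln 0.45 / ln 0.60 = 1.5632, as stated ("which yielded an expected hazard ratio of 1.5632"). This gives 177 events; at a mean event rate of 0.50, N = 354, an exact match.
- 40% v 60%: HR = ln 0.40 / ln 0.60 = 1.7937, which gives 103.5 events. At a mean rate of 0.533, N = 194 before rounding, against 196 stated.
- At N = 210 the same formula gives 83.0% power for 60% (112 events) and 57.8% for 55% (105 events).

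No covariate enters these figures, so the stated 80% does not depend on adjustment.

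**Step 2: power with and without the extra covariates.** The document gives no effect size for age or hyperinflammation, so a range was simulated, with 2000 trials per row. Improvement times were exponential and follow-up ended at day 15. Deaths without improvement stay at risk to day 15, so with complete follow-up Fine and Gray equals a Cox fit on that time scale. Overall improvement rates were held at the planned values. Hyperinflammation prevalence was assumed to be 50%. Two sets of runs were made: set A assumed a hazard ratio of 0.55 per day-0 rank and independent covariates; set B assumed exp(−0.5) = 0.61 per rank. Monte Carlo error in set A is about 0.9 point per figure.

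| Set | Assumed HR per SD of age / for hyperinflammation | N = 210, 40% v 60%: day-0 only → plus both | N = 354, 40% v 55%: day-0 only → plus both |
|---|---|---|---|
| A, none | 1.00 / 1.00 | 82.9% → 82.6% | 80.6% → 80.3% |
| A, weak | 0.85 / 0.80 | 85.1% → 85.4% | 80.0% → 80.5% |
| A, moderate | 0.70 / 0.60 | 84.3% → 89.2% | 82.1% → 86.1% |
| A, strong | 0.55 / 0.40 | 82.0% → 93.0% | 80.9% → 91.0% |
| B, weak | 0.82 / 0.74 | 81% → 83% | not run |
| B, moderate | 0.74 / 0.61 | 82% → 86% | not run |
| B, strong | 0.67 / 0.50 | 82% → 88% | not run |

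The strong rows differ (6 v 11 points) largely because set A assumes stronger predictors. Both covariates were added together, so the table does not show how much each contributes.

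**Step 3: where the gain comes from.** In set A at N = 210, the mean treatment hazard ratio moves from 1.89 to 1.98 (moderate) and from 1.88 to 2.11 (strong). The mean standard error of its log does not fall: 0.221 to 0.223 and 0.221 to 0.224. For the strong case, ln 1.88 / 0.221 = 2.86 and ln 2.11 / 0.224 = 3.33. The test becomes more powerful because the conditional effect is larger, not because the estimate is more precise.

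**Step 4: chance imbalance.** With 70 v 140 patients and 50% prevalence, the standard error of the between-arm difference in prevalence is √(0.25/70 + 0.25/140) = 7.3 points. If allocation is not stratified by hyperinflammation, a difference above 10 points would arise in about 17% of trials. The article's allocation sections mention no stratification, though the full protocol may.

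**The case against.** The case against acting is substantial, and most of it stands.

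- The stated model is valid under randomization and already adjusts for baseline status on the scale that defines the endpoint. The two cumulative clinical-status analyses among the secondary endpoints use the same single covariate, so the plan is consistent. A reader might infer an error or a contradiction; there is none.
- A reader might also infer that the planned 80% power is not met. The documents do not support that: the 80% comes from an unadjusted test, and every day-0-only figure in the table is 80% or more.
- A reader might take the article to call age prognostic. It does not. Age appears only in the imputation list, which also contains the randomized treatment, so listing alone is not a prognostic claim. For the laboratory values, the claim concerns adverse outcome, not time to improvement given day-0 status.
- Chance imbalance does not bias a randomized comparison, and the confidence interval allows for it. The shift toward 1 is a difference in what is being estimated, not bias in the planned analysis.
- The gain depends on assumptions. Correlation between day-0 status, age and hyperinflammation would reduce it.

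What does not stand is the view that nothing need be done because separate analyses by hyperinflammation are planned. Those describe subgroups; they do not bring the covariate into the primary test. Nor is there a material power penalty: with no prognostic effect, power is unchanged within simulation error.

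**Conclusion.** The point holds as missed efficiency, not as a mistake. The primary model omits baseline hyperinflammation, for which the prognostic claim is in the text, and age, for which it is only an inference. At 210 patients and 40% v 60%, including both changes power by about 0 points if their added prognostic value is nil or weak (2 at most in the runs made), about 4 to 5 points if moderate, and about 6 to 11 points if strong. The document cannot say which case applies, because it gives neither predictor strengths nor the prevalence of hyperinflammation.

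**What to change.** Before any comparative look at the data, pre-specify in the primary Fine and Gray model, alongside day-0 status and treatment:

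- hyperinflammation at randomization (yes/no), from laboratory values taken before randomization and never from follow-up values;
- age, as a linear term.

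Add a simple rule for missing baseline laboratory values, because {20c} covers missing clinical status and D-dimer but not lymphocytes, ferritin or LDH. State that the treatment effect is then a subdistribution hazard ratio conditional on these covariates. Keep the currently stated model as a sensitivity analysis, so that the less conditional estimate is still reported. The planned analyses by hyperinflammation status stay as they are.

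The cost is a few sentences in the analysis plan, a more conditional estimand, and a little handling of missing baseline values. No new measurements are needed. The article says the analysis plan is still to be finalized before database lock; with unblinded staff and interim monitoring, the covariates should be fixed earlier than that.

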### Objectives {7}

The study objectives are adapted from the WHO master protocol that was proposed to streamline interventional studies in patients with COVID-19 [19, 20]. The overall objective of the DAWn study is to evaluate the clinical efficacy and safety of investigational therapeutic agents relative to the standard of care in patients hospitalized with COVID-19. Additionally, the effect of interventions targeting the host response modulation will be evaluated separately in a pilot phase by a primary laboratory endpoint (change in thromboinflammatory biomarkers), and clinical outcomes will be evaluated as a secondary outcome.

Secondary objectives are to evaluate the clinical efficacy of different investigational therapeutics as compared to one another or the control arm.

All DAWn studies will investigate the same primary and secondary endpoints, listed in the full protocol available in an appendix to this paper. The primary endpoint is time to sustained clinical improvement, defined as a sustained 2-point improvement on the 7-rank WHO clinical status scale (see appendix). The essential endpoints are summarized below:
Clinical severity defined as the time from day 0 to sustained clinical improvement (improvement of > 2 points vs. the highest value of days 0 and 1 and sustained for at least 3 days) or live discharge, whichever comes firstHost thromboinflammatory status (DAWn-Antico): D-dimer levels, CRP, ferritin, LDH levels, and interleukin profileOxygenation: incidence, duration, and oxygenation-free daysMechanical ventilation: incidence, duration, and ventilator-free daysHospitalization: duration, time to live after dischargeMortality (day 15, day 28, time to death)Safety of the interventions: serious adverse events (SAEs) and adverse events (AEs) graded as severe, discontinuation or temporary suspension of drug administration (for any reason), changes in laboratory parameters (complete blood count, renal and liver function)

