**Fig. 2 Fig2:**
[figure not shown]
Trial design

DAWN-AntiCo will start with a pilot phase powered to detect the biochemical response and will continue to detect the effect on clinical outcomes. In this trial, a superiority hypothesis will be tested with a two-sided type I error rate of 0.05. Secondary hypotheses will be tested in a non-hierarchical way. The statistical analysis plan will be finalized before the database lock.

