#### Analysis of the secondary endpoint(s)

Cumulative clinical status up to day 15 will be analyzed using a general linear model adjusted for clinical status on day 0. The treatment effect will be estimated by the difference of mean values between the groups.Cumulative clinical status recorded daily during the hospital stay and on days 15 and 19 will be analyzed using a proportional odds logistic regression model, adjusted for clinical status on day 0. The common odds ratio will estimate the treatment effect.All-cause mortality rates will be estimated by the treatment group using the Kaplan-Meier method. The resulting Kaplan-Meier curves will be compared using a log-rank test. The treatment effect will be estimated by the hazard ratio using a Cox regression.Time-to-event parameters with competing risk (time to clinical improvement, composite cardiac endpoint): event rates will be estimated using cumulative incidence functions (CIF), and the resulting CIF curves will be compared using Gray’s test. The subdistribution hazard ratio will estimate the treatment effect.Duration of hospital and ICU stay: both parameters will be analyzed as time-to-event parameters with competing risk, whereby the event of interest is discharged from hospital/ICU, and the competing risk is hospital/ICU death.Continuous normally distributed variables (e.g., QTc) will be analyzed using a 2-sample *t* test. Treatment effects will be estimated by the difference in mean values between the groups. If applicable, changes from baseline will be calculated. Comparisons between treatment groups will be made by performing an analysis of covariance (ANCOVA) on the post-baseline value, using the baseline value as a covariate.Continuous non-normally distributed variables (clinical status, NEWS score, duration of supplemental oxygen, duration of mechanical ventilation) will be analyzed using a Wilcoxon rank-sum test. Change in ordinal scale at specific time points will be compared using Wilcoxon rank-sum tests.The proportion of patients with D-dimer < 1000, ferritin < 1000, and LDH < 600 on day 6 and day 15 will be compared.The proportion of patients who develop hyperinflammation at days 3, 6, and 15; time to hyperinflammation.

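### The pilot D-dimer endpoint has two unranked analyses, the GEE does not account for deaths as stated, and the day-6 comparison leaves out baseline D-dimer

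*Protocol article*

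**What the plan says.** Outcomes {12} and Analysis of the primary efficacy endpoint make the pilot's primary endpoint the D-dimer level on day 6, with a null hypothesis of equal mean levels in the two arms. On the test, the latter section says only: "Means will be compared with appropriate statistical testing after checking for normality". It then refers to a statistical analysis plan to be completed before database lock.

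The missing-data section {20c} treats the same variable differently. Missing values are imputed up to death, a log transformation is optional, and then: "After imputation, to account for deaths before day 6, D-dimer data will be analyzed using a GEE model". The section does not say how this model relates to the day-6 comparison, and it names no baseline term.

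Sample size {14} plans the pilot on an unadjusted comparison, taking a mean of 1000 and an SD of 600. For 80% power against a difference of 500, it arrives at "a sample size of 51 patients (17:34 with 1:2 randomization"). The number to be enrolled is then raised to 60 (20:40).

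Baseline D-dimer is available, because hyperinflammation is assessed at baseline and D-dimer is one of its criteria (Trial design {8}). Baseline adjustment is used elsewhere. The Fine and Gray model for the clinical primary endpoint includes day-0 status, and the secondary-endpoint section specifies "analysis of covariance (ANCOVA) on the post-baseline value, using the baseline value as a covariate" for normally distributed continuous variables.

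**The concern.** Two different analyses are written down for one primary variable, and nothing says which one decides the pilot. This differs from leaving detail to the analysis plan, because the article itself states both. Each branch also answers a different question. A t test concerns a difference in means, a log-scale model a ratio of geometric means, a rank test a shift in distribution, and a GEE over time a trajectory or an average. The choice of test and scale depends on the observed data in an open-label trial.

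Second, the article presents the GEE as the remedy for deaths before day 6. It is not one. A patient who dies has no day-6 D-dimer, and imputation stops at death. The Background {6a} itself says that D-dimer predicts poor outcome, so those who die early would tend to have high values. Removing them lowers the mean of the arm that loses more patients and makes that arm look better.

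Third, the day-6 comparison makes no use of a baseline value that is already collected for a highly variable marker, in a pilot of 60 patients.

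**Working it through.** **Inputs from the article.** Mean 1000, SD 600, difference 500, allocation 1:2, "two-sided type I error rate of 0.05", power 0.8, pilot of 20:40. The article gives no baseline-to-day-6 correlation and no death rate by day 6; the values used for these below are assumptions, shown as ranges.

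**1. The plan's own figure.** Control-arm n = (1 + 1/2) × [600 × (1.960 + 0.842)/500]² = 16.95, rounded up to 17. The total is 3 × 17 = 51, an exact match. The normal approximation gives power 0.801 at 17:34; the noncentral t gives 0.785. The sample size is therefore that of an unadjusted two-sample comparison of raw day-6 means, and its arithmetic is sound.

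**2. How often would the stated hypothesis be replaced?** A normal distribution with mean 1000 and SD 600 puts Φ(−1000/600) = 4.8% of values below zero. With mean 500 it puts Φ(−500/600) = 20% there. Skewness is therefore foreseeable. In simulated lognormal data with mean 1000 and SD 600 at 20:40, a Shapiro check rejected normality in 96% of pilots, so the null on means would usually give way to a rank or log-scale one.

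Rejection rates when a t test is used if normality is not rejected, and a rank test otherwise:
- Identical distributions: 0.049.
- Equal means but SD 600 vs 300 (assumed): 0.175, against 0.109 for the t test and 0.063 for Welch's test. The rank test is then answering a different question from the stated null on means.

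**3. Deaths.** Assume no treatment effect, lognormal D-dimer (mean 1000, SD 600, so log-scale σ = √ln(1.36) = 0.5545), and a latent death risk with correlation ρ to log D-dimer. With death probability p and c = Φ⁻¹(1 − p):

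mean in survivors = 1000 × Φ(c − ρσ)/(1 − p)

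Example at ρ = 0.6. For p = 15%, c = 1.036 and the survivor mean is 1000 × Φ(0.704)/0.85 = 893. For p = 5%, c = 1.645 and it is 1000 × Φ(1.312)/0.95 = 953. The difference is about 60.

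| Deaths by day 6 (assumed) | ρ = 0.2 | ρ = 0.4 | ρ = 0.6 |
|---|---|---|---|
| 5% vs 2% | 7 | 15 | 24 |
| 10% vs 5% | 10 | 21 | 32 |
| 15% vs 5% | 19 | 39 | 60 |

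Entries are the amount by which the arm with more deaths shows the lower mean. A different death model (log-odds of 1 per SD of log D-dimer) gives 18, 28 and 52 for the three rows. The standard error of the difference at 20:40 is 600 × √(1/20 + 1/40) = 164, so the largest entry is 60/164 = 0.37 standard errors, or 60/500 = 12% of the target.

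**4. Baseline adjustment.** Residual SD = 600 × √(1 − ρ²), where ρ is now the assumed baseline-to-day-6 correlation; noncentral t at 20:40 and difference 500.

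| ρ | Residual SD | Power |
|---|---|---|
| 0 (unadjusted) | 600 | 0.849 |
| 0.2 | 588 | 0.863 |
| 0.3 | 572 | 0.880 |
| 0.5 | 520 | 0.933 |
| 0.7 | 428 | 0.987 |

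These are raw-scale figures. They show the direction and rough size of the gain, and are not the exact power of the log-scale analysis proposed below.

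**The case against.** Much can be said for the plan. An unadjusted comparison of randomised arms is valid, and chance imbalance at baseline is already covered by its 5% error. At 20:40 it exceeds its own 80% power target. With a low correlation the gain from adjustment is only 1 to 3 percentage points. All of this stands, so a reader should not infer that omitting baseline D-dimer biases or invalidates the pilot.

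Naming the test and scale is commonly left to the analysis plan, which is not shown. A reader might also infer that the normality check inflates the type I error. It does not when the two distributions are identical (0.049), and the excess seen elsewhere depends on an assumed inequality of variances. What remains is that the article's own wording lets the hypothesis depend on the data.

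The wording in Objectives {7}, "primary laboratory endpoint (change in thromboinflammatory biomarkers"), could be read as a third, conflicting endpoint. It is a brief summary phrase, while Outcomes, Sample size and the primary-analysis section agree on the day-6 level. The real tension is between the primary-analysis section and {20c}.

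Finally, the GEE could be read as using pre-death values without inventing later ones. That reading is possible, but it leaves the target among those who die undefined, so it does not justify saying that deaths are accounted for. Nothing in the GEE wording rules out a baseline term either, so the point on baseline applies to the day-6 comparison only.

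**Conclusion.** The point holds in three parts of unequal weight. The article gives two unranked analyses of the pilot's primary endpoint, with test and scale open to choice after the data are seen. Its statement that the GEE accounts for deaths before day 6 is wrong. The day-6 comparison forgoes a baseline covariate that is already in hand.

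The first two parts rest on the text alone; only their size needs assumptions. Under the ranges tried, bias from deaths is about 7 to 60 ng/mL, at most 0.37 of a standard error. The documents do not support the inference that early deaths could reverse the pilot's result; the fault is an undefined estimand and a mistaken rationale. The third part is lost efficiency: 85% power against 86% to 99%, depending on a correlation that the documents do not give. This should be corrected, but it does not undermine the pilot.

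**What to change.** Prespecify one primary pilot analysis: log D-dimer at day 6 with log baseline D-dimer as covariate, reported as a ratio of geometric means with its confidence interval, and with no normality pre-test. State explicitly that it applies to patients alive at day 6, because adjusting for baseline does not by itself deal with deaths. Add a prespecified worst-rank analysis in which deaths before day 6 rank worse than every observed value, or make that composite the primary analysis. Keep the GEE as supportive and delete the claim that it accounts for deaths.

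The cost is wording; no new data are needed. The result becomes a ratio and is no longer a difference in means, so it will not map directly onto the planning difference of 500. The sample-size statement can stay on the unadjusted raw scale as a conservative reference, labelled as such.
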